## Abstract

**Highlights:**

**Public health relevance—How does this work relate to a public health issue?**
Population aging in Latin America and the Caribbean is associated with an increased prevalence of frailty, functional decline, and fall risk, representing a major public health concern due to its impact on morbidity, mortality, dependency, and healthcare utilization.Falls among older adults are one of the leading causes of disability, hospitalization, and loss of autonomy, generating a substantial burden on healthcare systems, particularly at the primary care level.

**Public health significance—Why is this work of significance to public health?**
This study proposes an innovative intervention based on immersive virtual reality for dual-task training, simultaneously addressing motor and cognitive components that are critical for fall prevention and the maintenance of functional capacity in older adults.The implementation of the protocol within a community-based primary care setting allows for the evaluation of its feasibility under real-world conditions, contributing to the generation of applicable and scalable evidence for public health systems.

**Public health implications—What are the key implications or messages for practitioners, policy makers and/or researchers in public health?**
For healthcare professionals and policy makers, this study provides evidence on the potential integration of accessible technologies, such as virtual reality, into fall prevention programs and strategies aimed at promoting autonomy in older adults, supporting more engaging and personalized interventions.For public health research, the findings may inform future randomized controlled trials and the development of cost-effective intervention models, while addressing critical factors such as the digital divide, adherence, and implementation in community-based settings.

**Abstract:**

Aging is a progressive and heterogeneous biological process influenced by multiple factors that may compromise physical and cognitive capacities and increase the risk of frailty, functional decline, and falls in older adults. Falls represent a major public health concern due to their impact on independence and long-term care demand. Immersive virtual reality (IVR) delivered through active video games (exergames) has emerged as a preventive strategy that integrates sensory, motor, and cognitive stimulation within controlled and engaging environments, particularly where traditional programs face challenges related to adherence and individual adaptation. This study aims to determine the feasibility and implementation of an IVR-based program for falls prevention in older adults at risk of frailty in primary health care (PHC). A quasi-experimental pre–post design will be conducted with an intervention group (IVR/exergames) and a conventional control group, including a total sample of 40 participants (20 per group). The protocol comprises three phases: baseline assessment and IVR familiarization; a 12-week intervention delivered twice weekly; and post-intervention assessment. The primary outcome will be fall risk assessed using the Timed Up and Go (TUG) test. Secondary outcomes include physical performance (Short Physical Performance Battery, SPPB, and handgrip dynamometry) and psychological aspects related to falls (Falls Efficacy Scale International, FES-I, and Activities-specific Balance Confidence Scale, ABC). Feasibility indicators will include recruitment, adherence, retention, and cybersickness. A reduction in TUG time is expected, providing preliminary evidence on the feasibility of integrating IVR-based programs for falls prevention within PHC systems.

## 1. Introduction

According to the World Health Organization (WHO), aging is a progressive biological process associated with the accumulation of molecular and cellular damage across the life course, leading to a gradual decline in physical and cognitive capacities [1,2]. This process does not manifest uniformly across individuals, as aging trajectories and their progression are strongly influenced by the interaction of risk and protective factors accumulated over time [3]. Globally, it is projected that by 2030, one in six people will be aged 60 years or older, reflecting a profound demographic shift with significant implications for health and social protection systems [4]. In Latin America and the Caribbean, this demographic transition presents specific characteristics. According to United Nations estimates, by 2022, the region was experiencing a more accelerated population aging process compared with other world regions [5]. In this context, countries such as Uruguay and Chile are expected to be among the most aged in South America by 2030, posing substantial public health challenges in terms of functionality and quality of life among older adults [6]. In Chile, this transition is occurring at a particularly rapid pace, with 14% of the population aged 65 years or older and a life expectancy exceeding 81 years [7,8].

The increase in the average age of the population has been associated with a higher prevalence of chronic diseases and geriatric syndromes, particularly within a context characterized by high levels of sedentary behavior. This situation contributes to the development of conditions such as frailty, sarcopenia, and balance disorders, which represent key determinants of functional decline and loss of autonomy in older adults [9,10]. In this scenario, falls are recognized as a relevant indicator of frailty and functional impairment, constituting one of the leading causes of morbidity, loss of independence, and risk of institutionalization [11].

Falls among older adults represent a major public health concern due to their multiple short- and long-term consequences, including fractures, balance disturbances, and injuries requiring prolonged recovery processes. Beyond their physical impact, falls also generate significant psychological effects, such as fear of falling, kinesiophobia, progressive social isolation, and increased functional dependence [12]. Collectively, these physical, psychological, and social consequences create a cycle of progressive decline that negatively affects the quality of life of older adults. In response to this scenario, governmental organizations have developed various preventive strategies aimed at maintaining functional capacity and reducing fall risk among older adults [13].

Among these interventions, multicomponent therapeutic exercise currently represents the primary preventive approach, integrating muscle strength training, balance, gait, flexibility, and functional tasks oriented toward activities of daily living. This type of program has demonstrated positive effects in reducing fall risk, improving physical performance, and preserving functional independence, positioning itself as the standard intervention across multiple community and clinical settings [1,11].

However, despite their demonstrated effectiveness, the implementation of traditional exercise programs presents relevant limitations in real-world care settings. Several studies have reported challenges related to sustained adherence over time, decreasing motivation in response to repetitive routines, limited immediate feedback on performance, and constraints in the program’s ability to dynamically adapt to individual changes in performance, preferences, and functional status among older adults [11]. These operational barriers may compromise therapeutic continuity and, consequently, the magnitude of the benefits achieved.

In this context, considering these limitations, virtual reality (VR) has emerged as a tool with the potential to complement and expand traditional therapeutic exercise strategies. Its incorporation into geriatric rehabilitation not only enables the reproduction of motor tasks oriented toward falls prevention, but also allows for the simultaneous integration of cognitive, sensory, and emotional demands within interactive and safe environments [14,15]. Unlike conventional programs, in which exercise progression and adaptation typically rely primarily on clinical judgment and periodic adjustments, VR enables continuous modulation of difficulty levels, immediate performance feedback, and real-time adjustment of task variables according to the user’s response.

The main contribution of VR lies in its capacity to provide personalized therapeutic experiences through the controlled manipulation of variables within the virtual environment, such as stimulus speed, motor complexity, attentional demands, required range of motion, and level of visual or auditory support. This level of personalization enables real-time adjustment of task intensity and complexity in response to user performance, fostering an optimal level of challenge that promotes neuroplasticity, motor learning, and active engagement in the rehabilitation process [16,17]. In contrast to traditional exercise programs, where individualization may be limited by group-based structures or constraints in human resources, VR allows for interventions that are simultaneously standardized and adaptive, maintaining protocol consistency without compromising clinical sensitivity.

Several studies have demonstrated its effectiveness in falls prevention and in improving functional performance, coordination, and movement confidence, thereby contributing to the physical and emotional well-being of older adults [15,18,19]. Furthermore, exergames provide a motivating, engaging, and adaptable environment tailored to individual capacities, promoting therapeutic adherence and sustained participation in exercise programs [14,19,20].

Although the literature supports the use of immersive virtual reality in older adults, the overall strength of the available evidence remains moderate to low. This is mainly due to methodological limitations, such as small sample sizes, heterogeneity in intervention protocols, and the lack of long-term follow-up, which highlights the need for further research to strengthen and consolidate these findings [21,22].

The present study focuses on determining the feasibility and implementation of a protocol using immersive virtual reality (exergames) for fall prevention in older adults at risk of frailty. This approach incorporates the development of standardized protocols while maintaining an individualized perspective that considers the specific needs and characteristics of each older adult. In this way, the interventions become consistent and reproducible without compromising clinical flexibility.

In addition, the protocol considers relevant constraints faced by health care teams, such as limited time and resources, by offering an alternative that complements traditional therapies and contributes to enhancing their effectiveness through an evidence-based intervention. In line with this rationale, the present work aims to implement an immersive virtual reality protocol focused on fall prevention, integrating new technologies into functional rehabilitation processes.

Accordingly, this protocol establishes the theoretical foundations, clinical criteria, technical procedures, and evaluation parameters required to standardize its application, ensuring both the safety of older adults and the therapeutic effectiveness of the intervention.

In line with the background described above, the present study proposes the following hypotheses:

Primary Hypothesis

**H1:** 
*Older adults at risk of frailty who participate in the intervention will show a significant reduction in fall risk, as evidenced by an improvement in Timed Up and Go (TUG) test performance, compared with the control group.*

Secondary Hypotheses

**H2:** 
*Older adults in the experimental group will exhibit a significant reduction in concern about falling, as measured by the Falls Efficacy Scale–International (FES-I), compared with the control group.*

**H3:** 
*Older adults receiving the intervention will demonstrate a significant increase in balance-related confidence, as assessed by the Activities-specific Balance Confidence (ABC) Scale, compared with the control group.*

**H4:** 
*The experimental group will show a significant improvement in physical performance, reflected by higher scores on the Short Physical Performance Battery (SPPB), including static balance, gait speed, and chair stand performance, compared with the control group.*

**H5:** 
*Older adults in the experimental group will maintain handgrip strength, as assessed by handgrip dynamometry, compared with the control group, without evidence of significant post-intervention decline.*

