### 2.3. Sample Size

The sample size (*n* = 40) was calculated a priori for a mixed repeated-measures design with two groups (control vs. experimental) and two assessment time points (pre- and post-intervention). The calculation assumed a significance level of α = 0.05, a statistical power (1 − β) of 0.80, and an expected small-to-moderate effect size (f = 0.25), with an assumed within-participant correlation of 0.5 and a nonsphericity correction of ε = 1.0. Under these assumptions, a minimum of 34 participants was required, evenly distributed as 17 individuals per group. Considering the potential for participant attrition and to ensure an adequate sample for pre- and post-intervention analyses, an attrition rate of approximately 15–20% was anticipated. Therefore, a total of 40 older adults will be recruited, with 20 participants allocated to the experimental group and 20 to the control group. The flow of participants through each stage of the study will be presented using a adapted CONSORT flow diagram adapted for quasi-experimental studies (Figure 1).

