### 2.8. Statistical Analysis

Data analysis will be performed using IBM SPSS Statistics software, version 30.0. Prior to analysis, data cleaning and coding procedures will be conducted to verify the absence of errors, outliers, or missing values. All statistical analyses will be carried out using a significance level of *p* < 0.05 and a 95% confidence interval.

At an initial stage, a descriptive and exploratory analysis will be conducted to characterize the sample and examine the distribution of the study variables. Sociodemographic variables (including age, sex, educational level, and comorbidities) will be summarized using absolute and relative frequencies for categorical variables, and measures of central tendency and dispersion (mean, median, standard deviation, and interquartile range) for continuous variables. Normality will be assessed using the Shapiro–Wilk test. Based on distributional assumptions, between-group comparisons will be performed using the independent-samples *t*-test for normally distributed continuous variables, the Mann–Whitney U test for ordinal variables or continuous variables with non-normal distributions, and the chi-square test for nominal variables.

To evaluate the effects of the virtual reality intervention, a two-way repeated-measures ANOVA will be conducted to test group-by-time effects (group × time). The primary analysis will follow the intention-to-treat (ITT) principle. A minimum of 20 imputed datasets will be generated, and this number may be increased depending on the proportion of incomplete data. Effect sizes will be estimated using partial eta-squared (ηp^2^) and interpreted as small (0.01), medium (0.06), or large (0.14) [36].

To control for inflation of type I error across secondary endpoints, *p* values for the prespecified secondary outcome analyses will be adjusted using the Holm–Bonferroni sequential procedure. This method was selected because it appropriately controls the family-wise error rate in the presence of multiple comparisons while being less conservative than the traditional Bonferroni correction. The correction will be applied to the secondary outcomes FES-I, ABC, SPPB, and handgrip strength. For the primary outcome, unadjusted *p* values will be reported. For the secondary outcomes, both unadjusted and Holm-adjusted *p* values will be presented, together with effect sizes and 95% confidence intervals [37].

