## 3. Expected Results

Pre- and post-intervention assessments will be conducted across functional, physical, and emotional domains. These assessments will be administered by trained health care professionals who will not be involved in the delivery of the interventions, thereby ensuring the independence of the evaluation process. In both the experimental and control groups, a system of rotating evaluators will be implemented to enhance objectivity and minimize potential assessment bias.

In addition, an assessment blinding process will be implemented. Scoring batches will be randomized, and standardized training and inter-rater reliability protocols will be established. Evaluators will work with alphanumeric identifiers (IDs) and a coded temporal marker, so that pre- and post-intervention conditions will not be identifiable during the data analysis process.

The primary outcome of this study is a reduction in fall risk among older adults at risk of frailty, as measured by the Timed Up and Go (TUG) test. This change is expected to be more pronounced in the experimental group compared with the control group.

As secondary outcomes, the experimental group is expected to demonstrate a significant reduction in concern about falling, as measured by the Falls Efficacy Scale–International (FES-I), and an increase in balance-related confidence, assessed using the Activities-specific Balance Confidence (ABC) Scale. Improvements in physical performance are also anticipated, including static balance, gait speed, and lower-limb strength, as evaluated through the components of the Short Physical Performance Battery (SPPB), including the chair stand test. In addition, maintenance of handgrip strength, assessed through handgrip dynamometry, is expected. Taken together, these outcomes are anticipated to be more pronounced in the experimental group, reflecting the potential effects of the proposed intervention.

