The Short Physical Performance Battery (SPPB) includes three sequential performance-based tests administered over approximately 6–12 min: static balance (feet together, semi-tandem, and tandem), gait speed over 2 or 4 m, and the five-repetition chair stand tests [46].

The experimental group is expected to achieve a clinically meaningful increase of ≥1 point in the total SPPB score, with a small-to-moderate effect size (d ≈ 0.40–0.70), reflecting improved lower-extremity function and overall functional stability.

*Handgrip Dynamometry:*

Muscle strength can be assessed using various procedures; however, handgrip strength measurement has become one of the most used tools in epidemiological studies due to its ease of administration, high reliability, and low cost. These characteristics make it a relevant health biomarker, with wide applicability in both clinical settings and population-based research [47]. In Chile, a study conducted by Lera et al. evaluated 5255 adults aged 60 years and older, reporting muscle weakness cut-off points of ≤27 kg for men and ≤15 kg for women [48].

In the present study, handgrip strength will be measured at baseline and post-intervention to examine potential changes associated with the immersive virtual reality program. Stability or attenuation of decline in handgrip strength in the experimental group, compared with the control group, will be interpreted as reflecting preservation of overall muscular function within the context of fall risk prevention.

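### H5 counts the lack of a significant decline in grip strength as maintenance, but the planned test of difference, with no margin, cannot support that conclusion

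*Protocol article*

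**What the plan says.** H1 to H4 in the Introduction each predict a significant improvement over control. H5 differs. It predicts that the experimental group "will maintain handgrip strength, as assessed by handgrip dynamometry, compared with the control group, without evidence of significant post-intervention decline".

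Section 3 repeats the expectation: "maintenance of handgrip strength, assessed through handgrip dynamometry, is expected". Section 3.2 (Handgrip Dynamometry) settles the interpretation in advance: "Stability or attenuation of decline in handgrip strength in the experimental group, compared with the control group, will be interpreted as reflecting preservation". Sections 3.1 and 3.2 give numerical benchmarks for TUG, FES-I, ABC and SPPB. For grip they give only cut-offs for muscle weakness, with no bound on how much change still counts as stable.

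Section 2.8 names one efficacy analysis, a two-way repeated-measures ANOVA testing group × time. Grip is in the multiplicity family: "The correction will be applied to the secondary outcomes FES-I, ABC, SPPB, and handgrip strength". The same section promises effect sizes and 95% confidence intervals, describes the secondary outcomes as supportive and exploratory, and warns that small effects in them may go undetected.

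**The concern.** A claim that strength was maintained is a claim that any loss is too small to matter. To support it, the data must exclude a loss of a stated size. A test of difference asks whether zero can be excluded, and failing to exclude zero leaves meaningful losses open. H5 nevertheless makes the absence of a significant decline its sign of success.

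Under that criterion, the less informative the data, the more easily H5 is supported. Small numbers and noisy measurement work against H1 to H4 but in favour of H5. The comparison with control does not remove the problem. The control programme also contains strengthening exercise (Section 2.7.6), so a null interaction could equally arise because both arms lost strength together.

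At stake is a prespecified secondary conclusion. The primary TUG analysis and the sample size are not affected.

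**Working it through.** **Inputs from Section 2.3**
- "The calculation assumed a significance level of α = 0.05, a statistical power (1 − β) of 0.80"
- "an expected small-to-moderate effect size (f = 0.25), with an assumed within-participant correlation of 0.5"
- "a minimum of 34 participants was required, evenly distributed as 17 individuals per group"
- "an attrition rate of approximately 15–20% was anticipated", with 20 per group recruited

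**Assumed inputs.** The plan gives no grip SD and no expected decline. True declines of 0.3, 0.5 and 0.8 SD are therefore assumptions. So are correlations above 0.5.

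**Step 1: reproduce the plan's figure.** For the interaction, λ = f²·N·m/(1 − ρ), with m = 2 and df = 1 and N − 2.
- N = 34: λ = 0.0625 × 34 × 2 / 0.5 = 8.5, power 0.807.
- N = 32: λ = 8.0, power 0.781.

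The minimum of 34 is correct. In terms of change scores, λ = d²·n/2 with n = 17 per arm, so 8.5 = 8.5·d² and d = 1.0. The trial is sized to detect a between-group difference of 1.0 SD of change.

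**Step 2: unit of change.** SD of change = SD × √(2(1 − ρ)). At ρ = 0.5 this equals the SD of the measure, so a 0.3 SD decline is 0.3 SD of change. At ρ = 0.8 it is 0.3/√0.4 = 0.474 SD of change.

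**Step 3: within-arm paired t-test, two-sided 0.05.** H5's wording implies this test, but Section 2.8 does not list it. Noncentrality = d√n. For 0.3 SD, ρ = 0.5, n = 17 it is 0.3 × √17 = 1.24 against a critical value of 2.12, giving power 0.21. Chance that a true decline is not significant:

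| True decline | ρ | n = 17 | n = 20 |
|---|---|---|---|
| 0.3 SD | 0.5 | 79% | 75% |
| 0.5 SD | 0.5 | 51% | 44% |
| 0.8 SD | 0.5 | 13% | 8% |
| 0.3 SD | 0.8 | 55% | 48% |
| 0.3 SD | 0.9 | 26% | 19% |

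**Step 4: planned between-group test, two-sided 0.05.** With two groups and two time points, the group × time test is a two-sample t-test on change. Noncentrality = d√(n/2). For 0.3 SD, ρ = 0.5, n = 17 it is 0.3 × √8.5 = 0.87 against 2.04, giving power 0.14. Chance that a true deficit against control is missed:

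| Deficit | ρ | n = 17 per arm | n = 20 per arm |
|---|---|---|---|
| 0.3 SD | 0.5 | 86% | 85% |
| 0.5 SD | 0.5 | 71% | 66% |
| 0.8 SD | 0.5 | 38% | 31% |
| 0.3 SD | 0.8 | 73% | 69% |

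These figures are before Holm adjustment.

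**Step 5: what the interval could exclude.** The 95% CI half-width for the between-group difference in change is t × √(2/n) SD of change.
- n = 17: 2.037 × √(2/17) = 0.70.
- n = 20: 2.024 × √(2/20) = 0.64.

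Even with an observed difference of exactly zero, a deficit of about 0.64–0.70 SD of change would remain compatible with the data. For comparison, a non-inferiority test (one-sided 0.025, 80% power, true difference zero) needs about 63 per group for an assumed margin of 0.5 SD of change and about 175 for 0.3 SD.

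**The case against.** The other side has real points.

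- **The plan is cautious.** Section 2.8 calls the secondary outcomes exploratory, admits that small effects may be missed, and promises confidence intervals. A reader might infer that the plan treats a null result as proof of maintenance. It does not go that far. But the caution does not withdraw H5's criterion, and nothing links the H5 conclusion to the interval.
- **Part of the claim is testable.** Attenuation of decline relative to control, in Section 3.2, is a difference in change, and the planned interaction addresses it directly. That part stands. The objection is to the stability reading and to the closing clause of H5.
- **Section 3.2 states no p-value rule.** This is correct. The significance criterion comes from H5 alone, and Section 3.2 adds the stability reading.
- **A real decline would not always be missed.** A reader might infer that it would usually be reported as preservation. That depends on an assumed decline and correlation. On the within-arm test, a 0.8 SD decline is missed in only 8–13% of trials at ρ = 0.5, and a 0.3 SD decline in 48% at ρ = 0.8 with 20 people.
- **Holm.** A reader might infer that a larger adjusted p value would be presented as stronger maintenance. The plan does not say so, and it reports unadjusted values as well.

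**Conclusion.** The point holds as a defect of inference. Followed as written, H5 and the stability reading in Section 3.2 let a non-significant result count as maintained grip strength, and no planned analysis can support that.

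Its practical size depends on assumptions. For a 0.3 SD loss at the plan's ρ = 0.5, the within-arm decline is non-significant in 75–79% of trials and the between-group deficit is missed in 85–86%. The size of the loss is assumed, and the within-arm figure belongs to a test that H5 implies but Section 2.8 does not list. Larger losses or a higher correlation reduce these rates. They do not turn a test of difference without a margin into evidence of maintenance.

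This is worth correcting, but it concerns one secondary hypothesis and does not touch the primary result.

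**What to change.** 1. Restate H5 as a between-group difference in change in grip strength.
2. Delete its closing clause on the absence of a significant decline, and bring the expectation in Section 3 into line.
3. In Section 3.2, delete the stability reading and keep attenuation of decline compared with control.
4. In Section 2.8, say that grip will be interpreted from the estimated difference in change and its 95% CI, both already planned, and that a non-significant result will not be read as maintenance.

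This costs a few sentences and no participants. The price is that the study can no longer claim maintenance from a null result. Adding a non-inferiority margin instead is not practical here, because at 17–20 per arm the interval could exclude only a deficit larger than about 0.64–0.70 SD of change when the observed difference is zero.
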